### Follow-Up Procedure and Data Monitoring

The research team will monitor incoming data to ensure that the app is functioning correctly. The research team will not contact participants outside automatic messaging of the app unless they reach out to the research team with queries, for example technical issues, or if they are unsure of how to perform a task with the app.

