#### Exclusion Criteria

Participants will be excluded if they are listed as being *red* risk by Combat Stress, which is determined by the clinical team following an initial assessment and is based on a traffic light system to assess risk, where red indicates an immediate high risk to the individual and/or others. *Red* risk is applied independently of the research team and is used only where participation in the study could impact clinical treatment. The exclusion applies only during the contact list data extraction. Participants will be excluded if they do not have a mobile phone or have not given the Combat Stress consent for contact for research purposes.

A power calculation was performed based on previously reported data from Combat Stress [11,46]. This study requires a sample of 37 participants in each arm, with an 80% power to detect with a probability of 5% mean change in alcohol consumption of 4 UK units (approximately 40 g of alcohol per week, 10 g per unit) between control and intervention arms, at 3-month follow-up (day 84). Four units have been selected based on these 2 criteria: (1) reductions observed in similar studies [4,8,22,24,47] and (2) reductions observed in the feasibility trial of *Drinks*:Ration, which found a 7 UK-unit decrease at week 4. We aim to invite a minimum of 620 veterans to participate in the study to account for a 30% acceptance of invitation and 40% attrition rate.

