### Recruitment

This study will recruit participants through Combat Stress (established in 1919), a third-sector charitable organization that provides mental health services, including substance misuse to UK veterans. It is the largest military charity in the United Kingdom in terms of the number of individuals treated, providing both inpatient and outpatient secondary mental health services to veterans and specializing in PTSD. Since 2011, Combat Stress has been funded by the NHS in the United Kingdom to provide a national specialist PTSD clinical service for veterans [48]. Combat Stress facilitates access to eligible participants and jointly with King’s College London oversees any risks that arise as a result of participation in the study. It is important to note that although this study uses a sample of veterans from Combat Stress, it is hoped that *Drinks*:Ration will be useful for the wider veteran community.

Potential participant contact details (postal address and/or email if available) will be extracted from the Combat Stress Patient Management System for those who meet the study eligibility criteria and who have provided consent to be contacted for research purposes. Only those who have had contact with Combat Stress over a 2-year period between January 1, 2018, and December 31, 2019, will be contacted. It is estimated that about 3000 patients with Combat Stress are eligible to be contacted by the research team.

Where contact details are available, eligible participants will be invited to take part via email in the first instance. The first contact will include an explanation of the study, link to the participant information sheet, and instructions on how to download *Drinks*:Ration using a unique quick response (QR) code. Once participants have downloaded the app, they will be invited to report alcohol consumption using TLFB for alcohol consumption [43] for the last 7 days and confirm the military serving status (to validate eligibility). Those meeting the study eligibility criteria will be invited to register an account and complete the baseline questionnaire (day 0).

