The app is compatible with all modern iOS- and Android-supported devices, and no involvement of the research team is required for participant enrolment. Data is collected, managed, and processed using the Google Firebase server infrastructure in London, United Kingdom.

In this study, the intervention arm will receive the app with all functionalities, including push notifications and SMS text messaging. The control arm participants will have access to only the *questionnaire and feedback* module and will not receive any form of personalized messaging, except prompts to complete questionnaires and reminders to review alcohol consumption feedback (see the Message section for more information). Participants in both arms will complete additional questionnaires on their mood and general mental health when responding to the weekly questionnaires. These responses will be used to personalize the content of the app and push notifications and SMS text messaging delivered to the intervention arm only.

Participants in both arms will be asked to use the app for 28 days. After which, they can continue to use the app; however, they will not receive personalized messaging, and the data collected after this point will not be used in the analyses. However, participants will receive a reminder message on day 84 and day 168 to complete questionnaires.

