### Messaging: Push Notifications and SMS Text Messaging

In addition to the *Drinks*:Ration app, participants will receive personalized push notifications and SMS text messaging that provide prompts to use the drinks diary, complete questionnaires, suggest alternative behaviors, provide feedback on goals, and promote a healthy lifestyle. A bank of personalized messages (both for SMS text messages and push notifications) informed by 180 tailored messages developed previously (which are informed by the Health Action Process Approach framework and targeted toward specific BCTs) [49] will be used.

*Drinks*:Ration uses baseline and contiguous measurements (day 7/14/21) to inform the type of message a participant receives to provide an individual participant-centric approach. Baseline measurements are used to identify suitable messages, *and as a participant engages with Drinks*:Ration, continuous measurements, including questionnaires (baseline and weekly questionnaires) and the drinks diary, are used to reflect current behavior and attitude. The messages cover a wide range of topics to target beliefs and motivations, with the primary aim of increasing the participant’s awareness of their drinking habits and behaviors. The messages are divided into 3 categories:

Tailored: personalized to drinking habits, baseline, and weekly questionnaires;Tailored and triggered: tailored to baseline and contiguous measurements and a specific event occurring; andTargeted (generic): sent on specific days to highlight inactivity, as a reminder to complete a questionnaire, or to alter participants to a new feature.

A participant can receive a maximum of 20 messages over the 28-day period, with a maximum of 2 messages in a single day. The system automatically decides when a message should be sent and the mode of delivery (push notification or SMS text messaging). A list of targeted (generic) messages to be sent to participants is defined in Table 1; except the messages listed in this table, participants in the control arm will receive no other messages. Participants in both arms will receive a generic message designed to promote retention of the *Drinks*:Ration app to allow for follow-up data collection. This will be sent monthly.

**Table 1 table1:** A list of targeted (generic) messages and the day on which they are sent.

Day	Message content	Study arm

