### Study Withdrawal and Consent

Informed consent will be sought from all participants via the *Drinks*:Ration app before the collection of any personal data, and they will be informed from the outset that they can withdraw from the study at any time. Individual optional consent (screenshots presented in Figure 2) will be sought for access to the GPS location, sending of push notifications, or SMS text messaging. In addition, to promote open science, consent will be sought from participants to share their data anonymously for research purposes. These data will be released upon completion of the study. Only the questionnaire response, remote measurement technology data, and alcohol consumption statistics will be shared. All data will be deidentified, and no personal data will be released. Participants can change optional consents at any time via the *settings* page of the app until analyses are performed at which point data will be extracted and analyzed.

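### The day-84 primary outcome is prompted once, by push or SMS that participants may refuse or switch off, with no other outreach, so some outcomes may be lost avoidably

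*Protocol article*

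**What the plan says.** All references are to the protocol article.

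- **Prompt.** The Intervention section says that "participants will receive a reminder message on day 84 and day 168 to complete questionnaires". Table 1 has one day-84 row, for both arms, and no repeat to non-responders.
- **Channel.** The Messaging section has the system choose between push notification and SMS. It describes no third mode.
- **Consent.** Study Withdrawal and Consent lists separate optional consents, among them "sending of push notifications, or SMS text messaging". It adds: "Participants can change optional consents at any time via the" settings page. Outcome prompts are not distinguished from intervention messages.
- **Other outreach.** Follow-Up Procedure and Data Monitoring says "The research team will not contact participants outside automatic messaging of the app", except when a participant comes to the team with a query.
- **Message load.** "A participant can receive a maximum of 20 messages over the 28-day period", but controls receive only what Table 1 lists. Both arms also get a monthly message meant to keep the app installed for follow-up (days 56, 112 and 140).
- **Other contact details.** Under Recruitment, postal address and/or email is extracted where available, and "eligible participants will be invited to take part via email in the first instance". No section uses either for follow-up.
- **Delivery failure.** The Discussion foresees that some participants will not be able to receive notifications. It answers with device testing and in-app feedback, not a second channel.
- **Analysis.** The Statistical and Data Analysis Plan keeps those lost in an intention-to-treat analysis, with multiple imputation where appropriate and repeated-measures mixed models.

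**The concern.** The channel that delivers part of the treatment also collects the primary outcome, and one consent setting governs both. A participant who tires of the messages and turns them off also turns off the day-84 prompt, and the stated rules offer no way to reach that person. The plan already expects 40% attrition on a self-reported outcome, so some of that loss may come from the contact rules rather than from unwillingness to answer.

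Message load and app content are part of the contrast between arms, so the chance of losing the outcome could depend on allocation. Intention-to-treat settles how non-use of the app is handled, but it does not supply a day-84 value that was never collected.

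**Working it through.** **1. Who goes unprompted.** Read together, the rules are: one message on day 84; push or SMS only; each optional and revocable; no other outreach. A participant is unprompted if both channels are refused or disabled, or if delivery fails. Refusing one channel is not enough, because the consents are listed separately and a mobile number is an inclusion criterion. The monthly messages travel the same way and do not reach this group. Contact after an adverse event and the debrief of 20 participants fall outside the rule, but neither is described as collecting the day-84 drinking record.

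**2. Message load to day 28, from Table 1.** Control: days 0, 7, 14, 21 and 28, so 5 messages. Intervention: days 0, 2, 13, 14, 18, 21, 23 and 28, so 8 generic messages, plus personalized ones up to the cap of 20. The cap is a maximum, not an expected load.

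**3. The plan's own sample size.** It states: "This study requires a sample of 37 participants in each arm, with an 80% power to detect with a probability of 5"%, for a "mean change in alcohol consumption of 4 UK units" between arms. No SD is given, so 37 cannot be computed forward. Solving backward (two-sided 5% assumed, normal approximation):

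SD = 4 / [(1.960 + 0.842) × √(2/37)] = 6.14 units (6.06 with the t distribution).

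**4. Is power at risk?** Enrolled = 620 × 0.30 = 186, or 93 per arm. Completers per arm = 93 × (1 − attrition). Power uses SD 6.14 and a difference of 4 units.

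| Attrition | Completers per arm | Power |
|---|---|---|
| 30% | 65 | 96% |
| 40% | 56 | 93% |
| 50% | 46 | 88% |
| 60% | 37 | 80% |

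Completers fall to the required 37 per arm only at about 60% attrition. At 40%, 186 × 0.40 ≈ 74 primary outcomes are missing. Each 10 points of attrition avoided recovers 186 × 0.10 ≈ 19.

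One caution: 620 does not follow from the stated inputs. 74 / 0.60 / 0.30 ≈ 411, whereas 74 / (0.30 × 0.40) ≈ 617, which treats 40% as the share retained. That is a separate matter. Under that reading the slack disappears, but the trial still has its planned 37 per arm.

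**5. Possible bias, illustration only.** Let D be how much worse non-responders' mean change is than responders' (taken as equal in both arms), and m_I and m_C the loss in each arm. The responders' contrast then shifts by (m_I − m_C) × D in absolute size. All inputs here are assumed.

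| Difference in loss | D = 4 | D = 8 |
|---|---|---|
| 0 points | 0 | 0 |
| 10 points | 0.4 units | 0.8 units |
| 20 points | 0.8 units | 1.6 units |

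The sign depends on which arm loses more. These shifts apply to a complete-case contrast, which is not the planned analysis.

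**The case against.** Running the trial without team involvement is a deliberate choice under Study Design, and reminder detail is often left to a fuller document. The monthly messages show that retention was considered. A participant must lose both channels to be unreachable, and can still open the app unprompted. Imputation and mixed models are planned, and day-28 drinking is available in both arms to inform them. Email is held only if available, and nothing shows it linked to the app account.

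Most of this stands, and it limits the point. It does not remove it. The contact rule and the optional consents are stated rules, and following them leaves some participants unprompted. The analysis methods protect only if data are missing at random given what was observed. That may fail if people silence messages for reasons tied to their later drinking.

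A reader might go further in three ways that the documents do not support.

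- **A power shortfall.** With 62 enrolled per arm (37 / 0.60), attrition of 50%, 40% and 30% would give power of 72%, 80% and 86% (SD 6.06). But the plan's own invitation and acceptance figures imply 93 per arm.
- **More loss in the intervention arm.** More messages could provoke opt-out, but controls have only the questionnaire and feedback module and less reason to keep the app. No arm-specific rate is given.
- **A known bias of 0.4 to 0.8 units.** That is a responders-only figure on assumed inputs, and it is zero if loss is equal across arms.

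**Conclusion.** The point holds as a matter of completeness and possible bias. On the stated rules, a participant without both channels gets no prompt for the primary outcome, and no other route is provided. How many this affects, and whether the arms differ, cannot be derived because no opt-out or delivery-failure rate is given. The effect on the planned estimate is likewise unquantified and depends on departure from missing at random.

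Power is not the issue on the plan's own figures: about 56 completers per arm and 93% power at 40% attrition, if 30% acceptance, the back-solved SD of 6.14 and a two-sided test all hold. The case for change rests on low cost, and on the fact that an uncollected day-84 record can later only be imputed.

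**What to change.** 1. **Study Withdrawal and Consent:** separate consent for study follow-up prompts (day 84, day 168 and the monthly retention messages) from consent for intervention messages, so that switching off the latter leaves the former on.
2. **Table 1 and Follow-Up Procedure and Data Monitoring:** allow a small fixed number of automated repeat prompts, for example two, to day-84 and day-168 non-responders. Send them by push/SMS, and by automated email where an address is held or is collected at registration. Use the same content and timing in both arms.
3. **Response window:** state it, for example 14 days, and record the completion date.

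This keeps the trial automated and leaves the intervention contrast unchanged. The cost is a small platform and consent change, including linking or collecting email addresses, and email will not reach everyone. Late responders' 7-day recall will fall somewhat after day 84, by up to two weeks under a 14-day window. The change should be made before recruitment starts.

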### Additional Data Collection

Additional data will be collected during this study for future research. Participants can opt out for additional data collection at any time.

#### Physical Activity Data Streams

Individual consent will be sought from participants at baseline (day 0) to collect physical activity data using Google Fit and Apple Health Application Programming Interface. The information to be extracted includes heart rate, distance travelled, activities, height, and weight. The aim of this study is to assess the feasibility of monitoring participants who consume alcohol at a hazardous or harmful level. The findings of this study will be reported elsewhere.

### Statistical and Data Analysis Plan

Statistical analysis will be performed after completing the data-collection phase. No interim analysis will be undertaken. The threshold for statistical significance will be *P*=.05, and effect sizes will be reported. Descriptive statistics (eg, demographics and response rate) and independent sample *t* tests and chi-square tests will be carried out to explore and identify potential differences between the intervention and control arms at follow-up. An intention-to-treat method will be used for primary outcome analysis such that those who are lost to follow-up will be retained in the primary analysis. Multiple imputation will be performed to estimate missing data, where appropriate. The primary outcome analysis will examine whether there is a statistically significant difference between the intervention and control arms on change in self-reported TLFB UK units consumed (as stated earlier, a difference of 4 UK units will be considered meaningful). Repeated-measures mixed modeling analyses will be conducted to examine the primary hypothesis that those who receive the full functionality of *Drinks*:Ration will report a greater reduction in alcohol consumption compared with control participants from baseline to 3-month follow-up (day 84). For the secondary outcomes, changes in the AUDIT score and WHOQOL-BREF computed quality of adjusted life years will be assessed using repeated-measures mixed modeling. These analyses will be repeated to assess changes between baseline and 6-month follow-up and will serve as a secondary outcome to assess the longer-term impact of the intervention on participants. These analyses will be reported as secondary outcomes.

For process evaluation measures, app utilization will be assessed using descriptive statistics of frequency of engagement using a previously published procedure [62]. This will include the number of times the app is initialized (started when not running in the background), the average session duration (time spent using the app overall and for each page), the number of times a participant performs an interaction (synchronize data, add a drink, or add a message rating), and the number of weeks in which participants remain engaged with the app. Participant engagement is defined as having at least 3 interactions in a 7-day period, other than receiving push notifications or SMS text messages, and will be used as a proxy for usability. An independent sample analysis will be carried out to explore and identify differences between the intervention and control arms. Usability of *Drinks*:Ration will also be reported using descriptive statistics and thematic analysis of *debrief* sessions. Finally, analyses will be carried out to identify differences between the intervention and control arms in app experience (as measured by MAUQ). In the pursuit of open science, data and code syntax will be published alongside reporting of the trial. As this is a single-blinded RCT, an independent researcher (who will be blinded to allocation) will review all analyses and data before publication. This study will be reported following the Template for Intervention Description and Replication [63] and CONSORT (Consolidated Standards of Reporting Trials) checklist [64].

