### Randomization and Blinding

Randomization occurs when a QR code is generated and a unique proxy identifier and participant gender are assigned. At this point, participants are automatically randomized to receive the control or intervention arm (see the Intervention section) and are blinded. Block randomization of size 2 will be used to ensure equal gender distribution across both conditions. The randomization procedure is carried out automatically by the *Drinks*:Ration platform with no human involvement, except to provide a proxy identifier and gender. The research team will be blinded to the randomization of the participant, except for DL, who led the development and will manage the *Drinks*:Ration app throughout the study.

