**Questionnaires (Multimedia Appendix 2)**															
	Informed consents		I^a^/C^b^		—^c^		—		—		—		—		—
	Sociodemographic		I/C		—		—		—		—		—		—
	Resource utilization		I/C		—		—		—		I/C		I/C		I/C
	Depression (PHQ2^d^) [53]		I/C		I/C		I/C		I/C		I/C		I/C		I/C
	Anxiety (GAD2^e^) [54]		I/C		I/C		I/C		I/C		I/C		I/C		I/C
	International Trauma Questionnaire for PTSD^f^ [55]		I/C		—		—		—		I/C		I/C		I/C
	Readiness to Change Ruler [56]		I/C		—		—		—		I/C		I/C		I/C
	Self-Efficacy Ruler [56]		I/C		—		—		—		I/C		I/C		I/C
	Alcohol Use Disorder Identification Test [57]		I/C		—		—		—		I/C		I/C		I/C
	World Health Organization Quality of Life-BREF [58]		I/C		—		—		—		I/C		I/C		I/C
	7-day Timeline Follow-Back for alcohol consumption [43]		I/C		—		—		—		I/C		I/C		I/C

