#### Outcome Measures

The primary outcome measure is the change between self-reported alcohol consumption as measured by the 7-day TLFB [43] over the previous 7 days between baseline (day 0) and 3-month follow-up (day 84). Participants will be asked to report how many drinks they consumed over the last 7 days as well as the type of drink they consumed on each day. Using the standard unit of measurements (Multimedia Appendix 3), weekly alcohol consumption will be determined by summing the number of units assigned to each drink. The TLFB has been extensively used to assess alcohol consumption and has demonstrated good test-retest reliability [43,60]. Secondary outcome measures will be (1) change in the baseline to follow-up AUDIT score and (2) change in the baseline to follow-up World Health Organization Quality of Life-BREF (WHOQOL-BREF) score to assess quality of adjusted life years. Process evaluation measures, following the model by Donabedian for evaluating quality of care [61], will be (1) app use (number of app engagement, screen views, and user retention) and (2) usability ratings as measured by the mHealth App Usability Questionnaire (MAUQ) [59]. A 3-month follow-up period was selected to assess the short-term benefits of the intervention on participants. The primary and secondary outcomes will also be reassessed at 6-month follow-up (day 168) to assess the longer term benefits of the intervention and will be reported as a secondary outcome.

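### The primary mixed model leaves open baseline handling, gender and the day-28 drinking measure; fixing them could save about 10–35% of variance at almost no cost

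*Protocol article*

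**What the plan says.** The Statistical and Data Analysis Plan section of the protocol article defines the primary question as "whether there is a statistically significant difference between the intervention and control arms on change in self-reported TLFB UK units consumed". The method is given in one sentence: "Repeated-measures mixed modeling analyses will be conducted to examine the primary hypothesis", covering baseline to day 84. The analyses are then to be repeated for baseline to day 168. The section commits to intention to treat, keeps participants who are lost to follow-up, and plans multiple imputation where appropriate.

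Three further items bear on this:

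- Under Randomization and Blinding: "Block randomization of size 2 will be used to ensure equal gender distribution across both conditions". The analysis section does not mention gender.
- Table 2 schedules the TLFB at days 0, 28, 84 and 168 in both arms. The analysis section gives day 28 no role.
- Under Intervention, on participants who keep using the app beyond 28 days: "the data collected after this point will not be used in the analyses".

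The article gives no standard deviation, no baseline-to-follow-up correlation, no gender mix and no expected day-28 response.

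**The concern.** A contrast defined on change, tested by a repeated-measures model from baseline to one endpoint and then rerun for a second endpoint, reads most naturally as a model with baseline among the responses. With complete data and baseline means left free in each arm, the arm-by-time term of such a model is the difference in mean change. In large samples that is never more precise than conditioning on baseline, and usually less.

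The requirement is small, 37 per arm, and 40% attrition is expected, so both precision and the handling of dropout matter. Day-28 drinking is an obvious candidate predictor of day-84 drinking among those who leave in between. An analysis that omits it relies on baseline alone to explain their missingness.

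Separately, the sentence under Intervention, taken literally, shuts out the day-84 primary outcome and the day-168 reassessment.

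**Working it through.** **The plan's own figure.** Inputs from the sample-size paragraph (under Exclusion Criteria): 37 per arm, 80% power, 5% significance, difference 4 units. Two-sided testing is assumed. No SD is given, so 37 can be neither confirmed nor refuted, only inverted: SD = 4 × √(37/2) / (1.960 + 0.842) = 6.14 (6.06 by the t distribution).

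**Change score against baseline adjustment, complete data.** With equal variances s² and correlation rho:

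- Change score: 2s²(1 − rho).
- Baseline-adjusted: s²(1 − rho²).
- Ratio, adjusted to change: (1 + rho)/2, so the loss is (1 − rho)/2.

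**With 40% of day 84 missing at random** and baseline-only participants kept in a likelihood model:

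- Adjusted, or baseline constrained equal: s²(1 − rho²)/0.6.
- Baseline as unconstrained response: s²(1 − rho²)/0.6 + s²(1 − rho)².

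At rho 0.5 these are 0.75/0.6 = 1.25 and 1.25 + 0.25 = 1.50 (in units of s²), a loss of 0.25/1.50 = 17%.

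| rho (assumed) | Loss, complete data | Loss, 40% missing | Power at 37 per arm if adjusted | Per arm for 80% if adjusted |
|---|---|---|---|---|
| 0.3 | 35% | 24% | 93.5% | 25 |
| 0.5 | 25% | 17% | 89.9% | 28 |
| 0.7 | 15% | 10% | 86.0% | 32 |

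The last two columns assume complete data and that 6.14 is the SD of a change score, which the article does not say. A simulation of 20,000 trials gave losses of 24%, 16% and 9% for the 40%-missing column.

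**Sensitivity to the variance ratio.** If the day-84 SD is k times the baseline SD, the complete-data loss is 1 − k²(1 − rho²)/(k² + 1 − 2·rho·k). At k = 1.5 it is 13% to 0.2% over rho 0.3 to 0.7; at k = 0.8 it is 50% to 37%.

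**Precision gain from day 28.** Let r be the correlation of days 28 and 84 given baseline, q28 the share answering at day 28, and 0.6 the share at day 84, with dropout monotone. The variance falls by r²(1 − 0.6/q28). With baseline correlations 0.6 and a day-28 to day-84 correlation of 0.8, r = (0.8 − 0.36)/(1 − 0.36) = 0.6875; at q28 = 0.9 the gain is 0.473 × 0.333 = 16%. If q28 is also 0.6 the gain is zero. Over assumed correlations of 0.3 to 0.8 and q28 of 0.6 to 0.9, the range is 0 to 16%.

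**Gender.** With a proportion p of women and a difference of d SDs, gender explains p(1 − p)d² of the variance. Assumed p of 0.03 to 0.10 and d of 0.25 to 0.8 give 0.03 × 0.97 × 0.0625 = 0.2% up to 0.10 × 0.90 × 0.64 = 5.8%.

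**The day-28 cut-off.** The sentence under Intervention follows a statement about continued app use, and the next sentence provides reminders for the day-84 and day-168 questionnaires. Outcome Measures and the analysis section both define analyses at those days. The literal text and the rest of the article disagree, but the context shows that app-use data were meant.

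**The case against.** The article never says that baseline is an unconstrained response. A mixed model with baseline means constrained equal fits the same sentence and loses about nothing. Baseline parameterisation, covariates, visits and imputation variables are details that a condensed article commonly leaves to a fuller plan, and nothing stated excludes gender or day 28. An unadjusted change contrast is also valid under randomisation. All of this stands: the point is an improvement to make, not an error in the primary test.

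The stakes may also be lower than 37 per arm suggests. On the article's own figures, 620 × 0.3 × 0.6 is about 112 completers if everyone who accepts is eligible. At an SD of 6.06, 56 per arm gives about 93% power without adjustment. Omitting gender tends to make the test slightly conservative rather than biased.

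A reader might go further and infer that the planned analysis is seriously biased by dropout. A simulated stress case can be built to show this: 62 per arm, correlations about 0.6, true effect −0.40 SD, and about 40% missing, driven by day-28 drinking in controls only. A baseline-adjusted completer analysis then gives about −0.29, which is (0.40 − 0.29)/0.40 = 28% too small, while imputation by arm with day 28 recovers −0.40. The documents do not support that reading. The comparator discards those lost, whereas the plan retains them and intends multiple imputation, which could use day 28. Nothing in the article establishes controls-only dependence. With the same dependence in both arms, similar simulations gave bias between nil and about 9%.

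**Conclusion.** The point holds as a near-free improvement to an under-fixed primary analysis. Under the weaker of the readings that the text permits, the loss is 35% to 15% of variance with complete data and about 24% to 10% with 40% of day 84 missing, for assumed rho of 0.3 to 0.7 and equal variances. Under a constrained-baseline reading it is about nil. The second range suits this trial better, given its planned attrition. The size moves with the variance ratio, but in large samples the direction does not reverse.

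Day 28 helps with bias only where dropout after day 28 depends on day-28 drinking and does so differently by arm, and only for participants who answered at day 28. It is useful protection, not a guarantee. Gender is a minor addition.

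A reader might also infer that the sentence under Intervention removes the primary endpoint from the analysis. Its context and the outcome and analysis sections show otherwise, so it is a secondary wording correction.

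**What to change.** Specify one mixed model for TLFB units, before any data are seen:

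- responses at days 28, 84 and 168;
- fixed effects for arm, visit, arm × visit, baseline TLFB, baseline × visit and gender, with unstructured covariance;
- the arm difference at day 84 as the primary contrast, and the day-168 difference from the same model as the longer-term result.

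An equivalent model with baseline among the responses and arm means constrained equal at day 0 would serve as well. It keeps baseline-only participants in the likelihood directly; the covariate form needs the planned imputation to keep them. Run any multiple imputation by arm and include day-28 TLFB.

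Separately, reword the sentence under Intervention so that the exclusion after day 28 covers only app-use and diary data, and state that the day-84 and day-168 questionnaires are analysed.

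The cost is wording and slightly more analysis work. Every variable is already scheduled for collection.
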